### Forecast execution dates

Initial recruitment of patients: September 2018.

Finalization of patient recruitment: April 2019.

Finalization of patient monitoring period: April 2020.

Publication of results: October 2020.

## Discussion

The presence of multimorbidity makes it difficult for patients to seek help, receive a conclusive diagnosis, receive quality care and adherence to treatment. The present study proposes the evaluation by means of a leading and novel intervention in the field of ICTs of disorders of high prevalence and producing great disability, such as the multimorbidity between depression and type 2 diabetes/chronic low back pain. In addition, in a PC setting, where these patients with a great need for healthcare provision are increasingly attended. The aim is to evaluate the effectiveness and cost-effectiveness of this treatment in the management of depression with medical comorbidity, as well as to achieve maximum impact for the Spanish National Health System, generating knowledge that can be included in the clinical guidelines for multimorbidity treatment in PC and throughout the health system.

It should be noted that this is the first study of its kind to use ICTs in the treatment of multimorbidity. It is also the first treatment for multimorbidity in Spain. This study has several strengths: it follows the guidelines of comorbidity treatment (Ariadne’s Principles); it will be conducted on a wide age range – most similar studies have been carried out on a geriatric population, but non-geriatric patients will also be included, facilitating preventive and health promotion aspects. In order to overcome one of the limitations described in meta-analyses preformed on previously published works, it includes a cost-effectiveness study; finally, the results obtained from this study can be easily transferred to the health system through the modification of the current management given to this group of conditions.

No particular difficulties are expected as regards the recruitment of patients with depression or their participation in the study. The negative attitudes of some GPs may hinder their recommending this treatment, therefore a training session on the study will be held at the participating PC health centres for professionals interested in participating. The main limitation of the study may be a significantly greater rate of dropouts in the treatment groups (40% in previous studies). Efforts will be made to maintain dropout rates in the range of 30% in order to overcome this limitation. In any case, an associated qualitative study will be included with this study to analyse the barriers and limitations of this therapy on Spain’s public health system. On the other hand, in addition to the intention-to-treat analysis, an analysis per protocol will be performed to determine the efficacy of the intervention in those patients who do not abandon the treatment.

The treatment programmes used in this study includes therapeutic strategies (mindfulness, healthy lifestyle habits, positive psychology and behavioural activation) that have proven their efficacy for depression, type 2 diabetes and chronic low back pain treatment [13, 14, 23, 24, 28]. Furthermore, this intervention will lead to improved financial sustainability, maximizing the use of resources and responding to principles of efficiency and effectiveness. In conclusion, the positive results of this study could have a significant impact on one of the most important problems in the health context: multimorbidity.

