### Randomization, allocation and masking of study groups

At such a time, the assessor will collect the baseline data and contact a person independent of the research group to perform the individual randomization and inform the assessor of a code that corresponds to the type of treatment (unknown by the assessor) and send it to the researcher with the baseline data. Another independent person will do the data monitoring with a general practitioner. The randomization will be conducted by blocks of patients from the three PC centres, with 100 patients selected from each centre so that 150 patients are randomized into each of the two arms. Participants agree to their inclusion before finding out the treatment to which they will be allocated. All participants will be free to withdraw from the treatment at any time.

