### Interventions

#### Internet-delivered psychological intervention

All interventions (except iTAU) comprise two face-to-face individual sessions and 6 online, individual and interactive therapeutic modules. Each face-to-face session will be 90 min in length. The online therapeutic modules are oriented to work on different psychological techniques, supported by multimedia material (videos, audio, etc.), as Internet support, and the duration of each module will be approximately 60 min.

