#### iTAU at primary care level

All the patients included in the study (whether they receive the Internet-delivered psychological intervention or not) will be also treated by their GPs. In practice, treatment-as-usual in PC is any kind of treatment administered by the GP to the patient with depression. However, this treatment in primary care will be improved because the participating GPs will receive a training programme on the widely used Spanish Guide for the Treatment of Depression in Primary Care, which is based on the NICE guidelines on subject [15]. In case of suicide risk, severe social dysfunction or worsening of symptoms, it is recommended that patients are referred to mental health facilities [38]. For both groups, the use of health and social services – including consultations with professionals, pharmaceutical use and other resources, will be registered using the Client Service Receipt Inventory (CSRI) [39].

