### Analysis strategy

#### Analysis of clinical efficacy

Intention-to-treat and per-protocol analysis will be used. Analysis will include the description and ‘head-to head’ comparison between the two groups. Descriptive statistics of the included variables (mean and 95% confidence interval for normally distributed quantitative variables; and median and interquartile range for abnormally distributed quantitative variables) will be performed. To confirm the main hypothesis, all variables will be compared (t0-tk) using an analysis of variance (ANOVA) and post-hoc tests or Kruskal-Wallis non-parametric tests. Finally, more sophisticated multivariate analysis, including multilevel regression, will be used. The effect size of improvement and the number needed to treat (NNT) in each arm will be estimated.

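### The per-protocol comparison is given an efficacy reading it cannot carry, because only the intervention arm has a programme to abandon

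*Protocol article*

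**What the plan says.** Under Analysis of clinical efficacy the article states: "Intention-to-treat and per-protocol analysis will be used". It adds: "Analysis will include the description and ‘head-to head’ comparison between the two groups". Neither analysis is named as the one on which the conclusion rests.

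The Discussion gives the per-protocol analysis its purpose. In addition to ITT, "an analysis per protocol will be performed to determine the efficacy of the intervention in those patients who do not abandon the treatment". The same paragraph names as the main limitation "a significantly greater rate of dropouts in the treatment groups (40% in previous studies", and sets a target of about 30%.

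The arms differ in what can be abandoned. Under Internet-delivered psychological intervention: "All interventions (except iTAU) comprise two face-to-face individual sessions and 6 online, individual and interactive therapeutic modules". Under iTAU at primary care level, "treatment-as-usual in PC is any kind of treatment administered by the GP to the patient with depression", and this GP care goes to both arms: "All the patients included in the study (whether they receive the Internet-delivered psychological intervention or not) will be also treated by their GPs". Under Randomization, allocation and masking: "All participants will be free to withdraw from the treatment at any time".

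**The concern.** Abandoning the programme happens after randomisation and is the patient's own choice. The programme runs 8-12 weeks, is largely self-directed, and depends on homework and reminder e-mails. Those who finish it may well differ in motivation and prognosis from those who stop.

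The iTAU arm has no matching event. A control patient can leave open-ended GP care or the study, but cannot stop a module programme that was never offered. The controls who would have completed are therefore not identified. Restricting the analysis to non-abandoners then compares two groups that randomisation did not form, and a difference between them is not the efficacy of the intervention in completers.

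At stake is how a discordant result would be read. If dropout is heavy and ITT is diluted, the article's wording allows a per-protocol difference to be reported as efficacy, although it could arise with no treatment effect.

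**Working it through.** **The plan's own figure.** Sample size gives a 0.5 SD difference, 80% power and 5% significance (two-sided assumed): n = 2 × (1.96 + 0.84)² / 0.5² = 62.8, so 63 per group. Then 4 × 63 = 252, and 252 / 0.85 = 297 after 15% loss, against 300 stated. This reproduces. The article gives no figure for the per-protocol analysis, so what follows is an illustration.

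**Inputs from the article.** 150 patients per arm; a 0.5 SD design effect; dropout in the treatment groups of 40% in previous studies and a target of about 30%; 15% loss in Sample size.

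**Inputs assumed.** (a) The dropout rate stands in for the share p of the intervention arm excluded for abandoning. (b) No controls are excluded. (c) Adherence and outcome are jointly normal with correlation ρ of 0.1 to 0.3, where positive means that adherers do better regardless of treatment. (d) There is no true treatment effect.

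**Formulas.**
- c = Φ⁻¹(p) and λ = φ(c) / (1 − p)
- bias b = ρλ, in SD
- completer variance v = 1 − ρ²λ(λ − c)
- SE = √(v / n_T + 1 / n_C), with n_T = 150(1 − p) and n_C = 150
- rejection = Φ(b/SE − 1.96) + Φ(−b/SE − 1.96)

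**Worked case, p = 0.40, ρ = 0.3.** c = −0.253 and λ = 0.386 / 0.60 = 0.644. b = 0.3 × 0.644 = 0.193. v = 1 − 0.09 × 0.644 × 0.897 = 0.948. SE = √(0.948/90 + 1/150) = 0.131. b/SE = 1.47, and rejection = 31.3%.

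| Excluded from intervention arm | Completers v controls | ρ | Spurious benefit (SD) | Share of 0.5 SD | Rejection with no effect |
|---|---|---|---|---|---|
| 15% | 128 v 150 | 0.1 | 0.027 | 5% | 5.6% |
| 15% | 128 v 150 | 0.3 | 0.082 | 16% | 10.6% |
| 30% | 105 v 150 | 0.1 | 0.050 | 10% | 6.8% |
| 30% | 105 v 150 | 0.2 | 0.099 | 20% | 12.3% |
| 30% | 105 v 150 | 0.3 | 0.149 | 30% | 22.1% |
| 40% | 90 v 150 | 0.1 | 0.064 | 13% | 7.7% |
| 40% | 90 v 150 | 0.2 | 0.129 | 26% | 16.3% |
| 40% | 90 v 150 | 0.3 | 0.193 | 39% | 31.3% |

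**What ρ means in practice.** The completer mean exceeds the arm mean by p times the gap between completers and abandoners. At p of 0.30-0.40 the table therefore corresponds to gaps from 0.064 / 0.40 = 0.16 SD to 0.149 / 0.30 = 0.50 SD.

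**Sensitivity to the assumptions.** At ρ = 0 the bias is zero and rejection is 5.0%. At ρ = −0.2 the bias reverses, to −0.10 SD (30% excluded) or −0.13 SD (40%). If equal shares of controls are removed, but for reasons unrelated to prognosis, the bias does not change; rejection is then 6.5-19.4% at 30% and 7.2-25.9% at 40%. The bias cancels only if control exclusions select on prognosis in the same way, and a different criterion gives no reason to expect that.

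**The case against.** The strongest reply is that the article never defines the per-protocol set for either arm. Such definitions are commonly left to the full protocol or analysis plan, and their absence here is no finding. A reader might infer that completers will be compared with a wholly unselected control arm and that benefit is therefore overstated. The document does not say that all iTAU patients are kept, and it lets every participant withdraw. It gives no prognostic gap between completers and abandoners, so neither the size nor the sign of the bias is established. That part of the objection stands.

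Two further parts also stand. The 30-40% is a dropout rate, which may mix stopping the programme with loss to follow-up; to the extent that it is loss to follow-up, missing outcomes affect ITT as well. And a reader might infer that per protocol is the article's answer to dropout, or could displace ITT. In fact the stated responses are retention efforts and a qualitative study, and per protocol is described as additional to ITT.

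The objection does not reach the stated purpose. The Discussion says the analysis will determine efficacy in those who do not abandon treatment. Whatever definition a fuller document holds for iTAU, it cannot be the same event as abandoning the programme, so restricting to non-abandoners gives up the protection of randomisation.

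**Conclusion.** The point holds as a matter of stated purpose: the article gives a causal efficacy reading to a comparison that cannot support one, and its Methods do not say that ITT carries the conclusion. Lopsided exclusion is probable on the article's own account, because only one arm has a programme and more dropout is expected there. Bias in favour of the programme is likely but not certain.

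The figures of about 0.05-0.19 SD (10-39% of the design effect) and about 7-31% false positives rest on three assumptions: 30-40% excluded from the intervention arm, none from iTAU, and a correlation of 0.1-0.3. They show what is possible and are not an estimate for this trial. The matter should be corrected, but it does not threaten the ITT comparison.

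**What to change.** 1. Under Analysis of clinical efficacy, name ITT as the sole basis for the efficacy conclusion.
2. In the Discussion, replace the claim that per protocol will determine efficacy with wording that makes it supportive and descriptive.
3. To address the effect in patients who would complete, add a complier-average causal effect as a sensitivity analysis. Use randomisation as the instrument and a completion threshold fixed in advance from platform records. Ethical aspects offers the programme to iTAU patients only at the end of the study, so non-compliance with the programme is planned to be one-sided. In its simplest form the estimate is the ITT difference divided by the proportion completing.

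The first two changes are wording only. The third is one model and has three downsides:
- **Wider interval.** With 60-70% completing, the standard error is about 1/0.70 = 1.43 to 1/0.60 = 1.67 times that of ITT. With outcomes on all 300, the ITT standard error is √(2/150) = 0.115 SD, which becomes about 0.16 to 0.19 SD.
- **Exclusion restriction.** The model assumes no benefit below the threshold. This is doubtful here, since the first session covers motivation and medication adherence and each module teaches separate skills. Partial benefit would inflate the estimate, so a low, any-use threshold should be reported as well.
- **Outcomes from abandoners.** The analysis keeps the randomised comparison only if patients who stop the programme are still followed up.

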## Abbreviations

ADA: diagnosis according to criteria of the American Diabetes Association
AES: Advanced Encryption Standard
CHEERS: Consolidated Health Economic Evaluation Reporting Standards
CSRI: Client Service Receipt Inventory
EQ-5D-3 L: EuroQol-5D-3 L
GPs: general practitioners
ICERs: incremental cost-effectiveness ratios
ICTs: information and communication technologies
ICURs: incremental cost-utility ratios
IDF: International Diabetes Federation
ISPOR: International Society for Pharmacoeconomics and Outcomes Research
iTAU: improved treatment-as-usual
MBCT: Mindfulness-Based Cognitive Therapy
MINI: Mini-International Neuropsychiatric Interview
NICE: National Institute of Clinical Excellence (UK)
NNT: number needed to treat
PC: primary care
RCT: randomized controlled trial
WHO: The World Health Organization
